### Statistical analyses and sample size

Analyses will be performed using the free software R. The effect of the intervention on primary and secondary measures over time will be appraised using a generalised linear mixed model (GLMM), and, specifically, a linear multiple regression model where time (T1, T2 and T3) and group (experimental and control) are the independent variables whereas the primary and secondary outcome measures are the dependant variables. To avoid overly optimistic estimates of the effectiveness of the experiment, an ITT (intention to treat) approach will be used, using the method of multivariate imputation by chained equations algorithm (MICE). Descriptive statistics such as means, standard deviations, and frequencies will be also calculated.

The sample size of the study has been estimated a priori using G-power 3 [35] based on the formula provided by Cohen [36]. It was revealed that a sample of at least 55 participants will need to be recruited to accomplish a power study of .805 at alpha = .05 and a medium size effect (.15). Considering the dropout rates in previous studies in our context [21], we will invite approximately 200 individuals to participate in the current study.

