**Methods:**

A two-armed randomized controlled trial will be conducted on an adolescent sample from the general population. The experimental group will use the intervention module (GGOC-AD) of a mobile app on the GGtude platform for 14 days whereas the control group will use a non-active module (GGN-AD) of said app. Primary outcome measures will be obsessional beliefs and obsessive-compulsive symptoms, and secondary measures will be self-esteem and emotional symptoms. Three assessment points will be conducted at baseline, post-intervention, and one-month follow-up. A linear multiple regression model with an intention to treat approach will be used. The expected total sample size will be 55 participants.

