**Discussion:**

We expect that the intervention group will show a reduction in obsessional beliefs and OCD-symptoms at post and follow-up in comparison with the control group. Additionally, we expect that the app will improve participants’ self-esteem. This study could provide an accessible mobile health tool to prevent OCD-related symptoms in adolescents.

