### Primary and secondary outcome measures

All measures will be completed at pre-, post- and follow-up assessment. Participants will also complete a sociodemographic data sheet (*see additional measures*). The primary outcomes measures will be:

*Obsessive Compulsive Inventory - Child Version* (OCI-R-CV) [27]. The OCI-R-CV is a self-report instrument that assesses the discomfort associated with obsessive-compulsive symptoms in children and adolescents between 8 and 18 years old. It consists of 21 items with a 3-point Likert scale (from 0 = “never” to 2 = “always”). The total score and the six subscales (Doubting, Obsession, Hoarding, Washing/Checking, Ordering, and Neutralizing) will be used in this study. The Spanish validation of the OCI-R-CV shows good psychometric properties [28].*Obsessive Beliefs Questionnaire - Child Version* (OBQ-CV) [29]. The OBQ-CV is a self-report questionnaire that assesses obsessive beliefs through 44 items with a 5-point Likert scale (from 0 = “strongly disagree” to 4 = “strongly agree”). In this study, we will consider the three subscales: a) Responsibility and threat estimation, b) Perfectionism and intolerance of uncertainty, and c) Importance and need to control thoughts, and the OBQ-CV total score. The Spanish adaptation presents good psychometric properties [30].

The secondary outcome measures will be as follows:

*The Patient Health Questionnaire for Depression and Anxiety* (PHQ-4) [31, 32]. This is a brief-screening to assess anxiety and depression symptoms. It is composed of 4 items evaluated with a 4-point Likert scale (from 0 = “never” to 3 = “almost every day”). The total score and the two subscales (anxiety and depression) will be used in this study. The Spanish validation shows good psychometric properties [33].*Single-Item Self-Esteem Scale* (SISE) [34]. The SISE is a self-report measure that determines the extent to which the sentence “I have a high self-esteem” describes participants on a 9-point scale, ranging from 1 (“not very true for me”) to 9 (“very true for me”). In this study, the SISE will be used as a self-esteem score, in accordance with the reliability and criterion validity reported by Robins et al. [34].

Additional measures:

*Sociodemographic data sheet:* The data required will be the following: age, gender, data about their school center (academic year, class group, and school center).

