### Data management

Data will be collected and managed in line with the Ethics Committee of Research in Humans of Universitat de Valènica. Participants will access the questionnaires using a unique personal identification number (ID), created beforehand. It is a code that ensures anonymity and does not allow participants to be identified. Their ID will be used to match the collected data. No other personal data is requested. Data from the questionnaires will be stored on a secure server of the Universitat de Valènica. In addition, persons who do not adequately answer the two control questions (e.g., “In this question, please check “always”) included in the questionnaires at each evaluation time will be eliminated from the data base.

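### The primary analysis is named as a mixed model and, in the same sentence, as a linear multiple regression; fitting the regression to three scores per student would give wrong error rates

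*Protocol article*

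**What the plan says.** Under Statistical analyses and sample size, the Protocol article says the effect of the intervention over time will be appraised with "a generalised linear mixed model (GLMM), and, specifically, a linear multiple regression model", in which "time (T1, T2 and T3) and group (experimental and control) are the independent variables". It names no participant effect, within-student covariance or group-by-time term.

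The abstract, under Methods, gives a single model: "A linear multiple regression model with an intention to treat approach will be used".

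The data are repeated measures. Primary and secondary outcome measures states "All measures will be completed at pre-, post- and follow-up assessment", and Data management adds "Their ID will be used to match the collected data".

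The hypothesis, in the abstract's Discussion, is a "reduction in obsessional beliefs and OCD-symptoms at post and follow-up in comparison with the control group".

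On sample size, the article says "a sample of at least 55 participants will need to be recruited to accomplish a power study of .805 at alpha = .05", with an effect size of .15 that it calls medium.

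**The concern.** The word that joins the two model names narrows the first to the second. A linear multiple regression is not a special case of a mixed model that keeps the mixed part. It has no random effect and no within-person covariance. With time as a predictor, each student supplies three rows, and ordinary regression computes its standard errors as if those rows came from different people.

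The text therefore gives two incompatible specifications for both primary outcomes, and an analyst could follow either and claim to have kept to the protocol. What is at stake is whether the standard error of the treatment effect is right. The direction of the error depends on which coefficient is read. It is too small for a group coefficient averaged over waves and too large for a difference between groups in change.

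**Working it through.** **1. The plan's own figure.** The inputs are N = 55, alpha .05, power .805 and effect .15 (Statistical analyses and sample size). The effect metric is not named; read as Cohen's f², the figure reproduces. For a linear regression with one tested predictor:

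- noncentrality λ = f² × N = 0.15 × 55 = 8.25
- critical F(1, 53) at .05 = 4.023
- power = P(F(1, 53; λ = 8.25) > 4.023) = 0.805

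At N = 54 the power is 0.798, so 55 is the smallest N that reaches .80. The sample size is thus a regression calculation with one row per participant and no within-student correlation.

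**2. Ordinary regression on three rows per student.** Assume equal variances and an equal correlation r between any two waves (compound symmetry), 1:1 allocation and complete data. The documents do not give r; the range .5 to .8 is assumed.

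- *Group term, time-plus-group model.* The true variance of the coefficient is (1 + 2r) times what regression assumes. The effective cutoff is 1.96/√(1 + 2r).
- *Group-by-T2 contrast (change from T1, between groups).* The true variance is (1 − r) times what regression assumes. The effective cutoff is 1.96/√(1 − r).
- *Power of that contrast* when a correct analysis has 80%: Φ(1.96 + 0.84 − 1.96/√(1 − r)).

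Worked at r = .5:

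- The group cutoff is 1.96/√2 = 1.39, so two-sided type I error is .166.
- The contrast cutoff is 1.96/√.5 = 2.77, so type I error is .006.
- Power is Φ(2.80 − 2.77) = .51.

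| r | Group term, type I error | Group-by-T2, type I error | Group-by-T2 power (80% if correct) |
|---|---|---|---|
| .5 | .166 | .006 | .51 |
| .6 | .186 | .002 | .38 |
| .7 | .206 | .0003 | .22 |
| .8 | .224 | <.0001 | .06 |

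**3. Simulation check.** There were 6000 runs per cell, with 28 students per arm (56 in all, for balance) and three waves. The effect in each row was set so that a correct analysis has about 80% power: standardized differences of 0.75, 0.67, 0.58 and 0.47. The comparator is the same group-by-T2 contrast as a participant random-intercept model gives in balanced data.

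| r | Group term, regression: type I | Group-by-T2, regression: type I | Group-by-T2, mixed: type I | Power, regression | Power, mixed |
|---|---|---|---|---|---|
| .5 | .164 | .008 | .048 | .51 | .81 |
| .6 | .199 | .002 | .051 | .38 | .79 |
| .7 | .211 | .001 | .049 | .22 | .79 |
| .8 | .233 | .000 | .050 | .07 | .79 |

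The simulation agrees with the algebra. The directions hold for any positive r. At r = .3 the formulas give .121 for the group term, .019 for the contrast, and 68% power in place of 80%.

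**4. Does N = 55 carry over to the mixed-model contrast?** Not automatically. In a two-group regression f² = .15 corresponds to a standardized difference of 2√.15 = 0.77. With a standardized difference of 0.5, the mixed-model contrast in the same simulation has power .46, .54, .66 and .84 for r = .5, .6, .7 and .8. The answer depends on a correlation that the plan does not state.

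**The case against.** The best defence is that the sentence is loose wording for a linear mixed model. It commits first to a mixed model for effects over time, and what follows may only name the linear member of that family with several predictors. Matching scores by ID fits that reading, abstracts shorten model names, and random-effect structure is often left to a fuller document. This stands in part. A reader might infer that the plan analyses the three scores as independent. No section says so, and a mixed model with a participant effect would avoid the error entirely. The missing covariance detail is not a fault in an article. The fault is that two different models are stated and nothing resolves them.

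The sample size is also weaker evidence than it may look. It matches a regression with one row per participant, which shows the regression framing but does not show that 165 (3 × 55) correlated rows will be pooled.

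It is also tempting to say that every p-value would be invalid. That goes too far. The inflated error belongs to the group coefficient of the additive model, which averages over baseline and is not the stated hypothesis. The contrast that does match the hypothesis would be conservative, so it costs power and does not add false positives.

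Finally, ordinary regression should not be set against a baseline-adjusted comparison at T2. Part of that gain comes from the baseline adjustment, so the fair comparator is the same contrast in a random-intercept model.

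**Conclusion.** The point holds as a contradiction in the specification of the primary analysis, with conditional consequences. The methods text and the abstract lean towards a model with no within-student term, and the article does not resolve the conflict. If the regression is what is run on the stacked scores, the simulated type I error is about 16% to 23% for the additive group term. For the group-by-time contrast it is below 1%, and power falls from 80% to between about 51% and 7%. These sizes rest on compound symmetry, complete data and an assumed correlation of .5 to .8; the directions need only a positive correlation. If the mixed model is fitted with a participant random effect, the distortion is absent. That the plan treats the scores as independent is a possible inference, not something the documents state.

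**What to change.** In the abstract's Methods and in Statistical analyses and sample size, replace the linear multiple regression with one model. It should be a linear mixed model with time, group and their interaction, and a participant random effect or an unstructured within-student covariance. Name the group-by-time contrasts at T2 and T3 as the test of the intervention. Then restate the power of 55 participants for that contrast under a stated within-student correlation, preferably over a range. The estimation method (such as REML) and the degrees-of-freedom method are optional details.

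The cost is a change of wording in two places plus one recalculation. Mixed models are already within the plan's own terms and R fits them. The recalculated power may be less favourable than .805, and it is better to know that before the data are analysed.

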Figure 1 depicts the trial design and times of assessment. Students will be recruited from public schools in the metropolitan area of Valencia (Spain). Researchers will invite different schools to participate in the study. After the education center agrees to participate, members of the research group will meet students in the designated classroom, provide information about the study, and invite them to participate. Students will then receive a sheet with information about the study and the informed consent for parents or guardians and the student. Finally, participants that explicitly agree to participate, provide the informed written consent, and meet the inclusion criteria will be randomized in two groups: the intervention group that will use GGOC-AD and the control group that will use the GGN-AD module. On weekdays, students will complete the app during school hours at a pre-arranged time with the education center in order to interfere as little as possible. At least two members of the research group will be available to assist in the assessment sessions (T1-T3) and monitor the use of the app in order to promote participants’ retention. Students will be asked to complete the app at home during the weekend. As shown in Fig. 1, on the first day of the study, participants will be requested to complete the baseline assessment measures (T1, pre-treatment) and download the GGtude platform app using their personal mobile device. It will be freely available from the App Store or Google Play. The intervention group will access the GGOC-AD module of said app and the control group will use the GGN-AD module. Users will carry out cognitive training for 14 consecutive days, completing approximately three levels per day. On the day that they finish the app (day 14), participants will be instructed to complete the assessment instruments again (T2, post-treatment). Finally, a one-month follow-up evaluation will be conducted (T3). Both groups will complete the outcome measures and the app at about the same time, using their personal mobile device. At all-time assessments, questionnaires will be completed by Lime Survey software in a designated classroom.

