### Randomization

All the participants will be randomly assigned to GGOC-AD (intervention) or GGN-AD (control) groups (allocation 1:1) with the randomizer.org platform (no block randomization). It will take place prior to the T1 assessment and will be conducted by a researcher not involved in the assessment and intervention procedure.

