## Discussion

This study aims to describe the protocol for a randomized control trial of a tailored module of a mobile app to challenge OCD-related maladaptive beliefs in adolescents. It responds to the need to design preventive strategies in OCD, with children and adolescents being a target population due to the prevalence rates of OCD and the history of subclinical obsessive-compulsive symptoms that often precede the full-blown disorder. The rationale and design of the GGOC-AD module focuses on maladaptive beliefs relevant in OCD, proposed as a cognitive vulnerability factor, that could lead to OCD development [37, 38]. In a clinical sample of children and adolescents, Coles et al. [29] showed that OCD symptom severity and interference was related to obsessive beliefs and Wolters et al. [39] reported that the degree of adscription of these beliefs differentiated patients with OCD from community controls. Recently, Pozza et al. [37], who examined whether maladaptive beliefs longitudinally predict OCD, showed that several beliefs (e.g., perfectionism, intolerance of uncertainty, threat overestimation) predicted the later development of OCD symptoms. This suggests the need to specifically target these dimensions for early detection and preventive programs. Considering the effectiveness of GGtude modules for OCD in addressing maladaptive beliefs [18, 21–23], our main hypothesis is that following the use of the GGOD-AD module, participants will exhibit a reduction in OCD-related maladaptive beliefs. Furthermore, we expect that this change will also lead to a decrease in the distress associated with OCD symptoms, as previously reported by Akin-Sari et al. [23]. We expect no changes in those dimensions after using the GGN-AD module in the control group.

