A secondary objective is to examine the effects of the GGOC-AD module on self-esteem. We hypothesize that participants who use the GGOC-AD module will show increased self-esteem levels following the intervention compared to their pre-intervention levels. We expect no changes in self-esteem after using the GGN-AD module in the control group. The emphasis on self-esteem is particularly relevant during adolescence, a critical period for identity development. Moreover, explanatory models of OCD have suggested the relevance of self-construction on OCD [40–42]. Indeed, Roncero et al. [21] reported improvements in self-esteem following the challenge of OCD-related maladaptive beliefs. In addition, we will evaluate the modules’ impact on emotional symptoms. This examination could help ascertain the module’s specificity in addressing OCD symptoms and related beliefs versus affective symptoms.

If the GGOC-AD module proves effective, it could be used as a preventive strategy for OCD. Firstly, the module could act as a protective mechanism against vulnerability factors of developing OCD, which also could have an indirect impact on its symptoms, constituting a universal prevention intervention. Moreover, the implementation of GGOC-AD in a formal educational context may have additional benefits. That is, the app is a user-friendly and accessible tool that could be easily administered in a developmentally natural environment. This would allow a large number of students to be involved regardless of their risk of OCD, as it is less stigmatizing for individuals and provides the opportunity to promote mental health in an educational setting. Finally, this initiative is intended not only to potentially prevent the escalation of OCD symptoms and for its early detection, but also to improve early intervention for this population, providing an accessible and cost-effective tool in accordance with a stepped-care approach for OCD treatment (NICE, 2005). In fact, research on a case study with an adult OCD patient suggests its effectiveness as a relapse prevention tool [24].

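### The stated model names only time and group, with the untreated T1 wave as an outcome, so read literally no coefficient is the treatment effect and the group coefficient gives two-thirds of it

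*Protocol article*

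**What the plan says.** The section on statistical analyses and sample size of the Protocol article gives one model for all primary and secondary outcomes. Its type is given as "generalised linear mixed model (GLMM), and, specifically, a linear multiple regression model". The predictors are then listed in full: "where time (T1, T2 and T3) and group (experimental and control) are the independent variables". The article names no product of group and time, no baseline covariate and no change score.

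Three other places fix what such a model would estimate:

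- **T1 is untreated.** Under Study design and procedure, on the first day "participants will be requested to complete the baseline assessment measures (T1, pre-treatment"), and the module is used over the following 14 days.
- **Arms are comparable at T1 by design.** Under Randomization, the ratio is "allocation 1:1" and, of the allocation, "It will take place prior to the T1 assessment".
- **The hypothesis is comparative.** The Discussion paragraph of the Abstract expects a "reduction in obsessional beliefs and OCD-symptoms at post and follow-up in comparison with the control group".

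The main Discussion words its expectations differently. For self-esteem, "participants who use the GGOC-AD module will show increased self-esteem levels following the intervention compared to their pre-intervention levels". For beliefs and symptoms in the control arm, "We expect no changes in those dimensions after using the GGN-AD module in the control group".

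**The concern.** The trial asks whether the arms differ after treatment. In a model with main effects of time and group only, and T1 among the outcome rows, the group coefficient is a single arm difference held constant over three waves. In one of those waves nobody has been treated. The time coefficients pool both arms. Neither is the quantity in the Abstract's hypothesis.

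If the analyst follows the sentence as printed, the main estimate for every outcome is pulled toward zero, and any chance difference between arms at T1 becomes part of it. If the analyst instead assumes an interaction was meant, the deciding contrast (T2, T3, or both jointly) is still unnamed and can be chosen after the results are seen.

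**Working it through.** **1. The plan's own figure.** Inputs from the sample-size paragraph: N = 55, alpha .05, effect .15 (taken as Cohen's f²), power .805. For a linear multiple regression, the noncentrality is f² × N = .15 × 55 = 8.25.

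- One tested coefficient, two-sided: .8051, .8048 and .8045 with 1, 2 and 3 predictors; .8039 with the 5 predictors of the full group-by-time model.
- Two coefficients tested jointly: .705 with 2 predictors and .703 with 5; 68 participants are needed for 80%.

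The stated .805 reproduces as a single-coefficient test. It does not show whether an interaction was intended, and it does not cover a joint 2-df interaction test.

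**2. What the group coefficient estimates.** Let the true arm differences be 0 at T1 (randomised, untreated), d2 at T2 and d3 at T3. With three complete waves per person, as multiple imputation supplies, and ordinary least squares or a random intercept:

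expected coefficient = (0 + d2 + d3)/3 = (2/3) × (d2 + d3)/2.

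With d2 = d3 = 0.5 this is 0.33. In 150 simulated trials of 56 participants with a true effect of 0.80, the additive coefficient averaged 0.52 (expected 0.533). The interaction contrasts averaged 0.81 at T2 and 0.80 at T3.

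**3. How far two-thirds holds.** With d2 = d3:

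- AR(1) covariance gives 0.60 (correlation .5) or 0.57 (correlation .7).
- One unstructured example gives 0.59.
- Unimputed dropout, assumed 30% by T2 and a further 20% by T3, gives 0.46 to 0.48.

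All of these shrink the estimate further. Relative to the T2 effect alone, the factor is 0.50 if the effect halves by T3 and 0.33 if it vanishes.

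**4. Chance imbalance at T1.** With equal variances and within-person correlation r, a T1 difference of x SD shifts the expected coefficient by (x + rx + rx)/3 = x(1 + 2r)/3. The standard error of the T1 difference at 28 versus 27 is √(1/28 + 1/27) = 0.27 SD. A one-standard-error imbalance therefore moves the coefficient by 0.27 × 2/3 = 0.18 SD at r = .5.

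**5. Power.** The article gives neither a standardised difference nor r, so both are assumed: d2 = d3 = 0.5, r from .5 to .8, 28 versus 27, two-sided .05, and standard errors that respect the repeated measures. With k = 1/28 + 1/27 = 0.07275:

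- Additive group coefficient: effect 2d/3, SE = √(k(1 + 2r)/3).
- T2-minus-T1 interaction contrast: effect d, SE = √(2k(1 − r)).
- T2 contrast adjusted for T1: effect d, SE = √(k(1 − r²)).

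Power is from the noncentral t distribution (53 df; 52 df for the adjusted contrast).

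| r | Additive SE | Power | Interaction SE | Power | Adjusted SE | Power |
|---|---|---|---|---|---|---|
| .5 | .220 | .318 | .270 | .444 | .234 | .556 |
| .6 | .231 | .294 | .241 | .530 | .216 | .623 |
| .7 | .241 | .274 | .209 | .652 | .193 | .722 |
| .8 | .251 | .256 | .171 | .821 | .162 | .858 |

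**6. Sensitivity.** Taking f² = .15 as d = 2√.15 = 0.775 (an assumed equivalence for two equal groups), power at r = .5 is .63 additive, .81 interaction and .90 adjusted. The order is unchanged. The interaction contrast falls below the additive coefficient only when r is under 5/14 = .36, from solving (4/9) × 3/(1 + 2r) = 1/(2(1 − r)).

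**The case against.** The strongest reply is that the sentence lists factors, not a formula. Naming the two factors of a repeated-measures design without writing their product is common shorthand. The same sentence says that the aim is to appraise the intervention's effect over time, and the Abstract's hypothesis is comparative at T2 and T3. Both point to group-by-time. This stands in part: the text does not exclude an interaction, so a reader who infers that the trial will certainly report an attenuated effect goes beyond the document. But the article introduces its model as the specific one and stops at two variables, and the reproducible .805 does not settle which model was meant.

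It can also be said that a condensed article may leave contrasts to a fuller plan. That would answer a complaint about missing detail. Here the article does state a model, and the model as stated does not fit its hypothesis.

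A reader might infer from the main Discussion that the trial will be decided by separate within-arm tests, improvement in one arm and no change in the other. The document does not support this. Those sentences are expectations, no such tests are planned, and the design is a superiority comparison with the control module. A fall in one arm and stability in the other is also the pattern that a group-by-time effect would show.

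Finally, setting the additive coefficient against the baseline-adjusted contrast alone overstates the cost of the missing term, because part of that gap is the gain from adjustment. At r = .5, going from .32 to .44 is due to the interaction contrast; going on to .56 is due to adjustment. Adjustment is a matter of efficiency, not a correction of bias.

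**Conclusion.** The point holds conditionally. As printed, the model has no coefficient that expresses the trial's hypothesis, and its group coefficient is two-thirds of the mean T2/T3 effect. That factor is exact with complete or imputed data under ordinary least squares or a random intercept; for the effect at a single wave it also needs d2 = d3. The other covariance and dropout cases examined gave more attenuation. The factor does not depend on the size of the effect.

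The power figures rest on an assumed difference of 0.5 and r of .5 to .8. Over that range the additive coefficient loses to the interaction contrast by .13 (.444 − .318) to .57 (.821 − .256). If group-by-time was intended, the attenuation disappears, but the term and the deciding contrast still need to be written down. Under either reading, adjusting for a T1 score that is already collected is the better analysis over the range examined. The sample-size figure is not wrong for a single-coefficient test.

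**What to change.** 1. Define the treatment effect as the between-group contrasts at T2 and at T3. Estimate them from a mixed model on T2 and T3 with T1 score as covariate, group, time and group-by-time, or from a constrained longitudinal model with a common T1 mean.
2. At minimum, if T1 stays as an outcome wave, add group-by-time and test its T2 and T3 contrasts.
3. Say which test the power statement refers to. At f² = .15 and N = 55, .805 holds for one coefficient; a joint 2-df interaction test has about .70 and needs 68 participants for 80%.
4. Word the belief, symptom and self-esteem hypotheses in the Discussion as between-group differences, to match the Abstract, and report within-arm changes descriptively.

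The cost is a few sentences in the plan and a changed model formula in R. No new data or visits are needed. The sample size is affected only if the joint test is chosen.

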## Methods

### Study design and procedure

A two-armed, parallel-design randomized controlled superiority trial will be conducted to evaluate the effectiveness of the GGOC-AD module intervention for adolescents compared to a non-active module (GGN-AD). The randomization procedure is described in detail in the subsection 2.5. The present study protocol complies with the Standard Protocol Items: Recommendations for Interventional Trials (SPIRIT) checklist.

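### The outcome model names only time (T1 to T3) and group; fitted literally, its between-arm term averages in the pre-treatment wave and does not measure the difference at T2 or T3

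*Protocol article*

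**What the plan says.** In the protocol article, Methods, Statistical analyses and sample size, the outcomes are to be analysed "using a generalised linear mixed model (GLMM), and, specifically, a linear multiple regression model" in which "time (T1, T2 and T3) and group (experimental and control) are the independent variables", "whereas the primary and secondary outcome measures are the dependant variables". The three times are defined under Study design and procedure. On the first day students "complete the baseline assessment measures (T1, pre-treatment"; on day 14 "participants will be instructed to complete the assessment instruments again (T2, post-treatment"; then "Finally, a one-month follow-up evaluation will be conducted (T3". Randomization is 1:1 and takes place before T1.

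The question the trial sets itself is a comparison between arms after treatment. Study design and procedure calls it a "randomized controlled superiority trial will be conducted to evaluate the effectiveness of the GGOC-AD module intervention". The abstract's Discussion expects that "the intervention group will show a reduction in obsessional beliefs and OCD-symptoms at post and follow-up in comparison with the control group". The main Discussion adds that no change is expected in the control arm.

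**The concern.** The hypothesis is that the arms start level and differ at T2 and T3. That is a difference in change, or equivalently an arm difference at each later wave. A model with one term for time and one for group has no parameter for it. Its group coefficient is a single arm difference assumed equal at all three waves, including the one before anyone has used the app.

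If that coefficient were reported as the intervention effect, three things would follow. A real effect would be understated. Any chance difference at T1 would enter the estimate with weight one third. An effect at T2 that fades by T3 could not be told apart from a smaller effect present at both.

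**Working it through.** **Inputs from the article.** N = 55; power .805; alpha .05; effect size .15; waves T1 (pre-treatment), T2 and T3; 1:1 allocation, so the expected arm difference at T1 is 0; multiple imputation, so the analysed data are balanced over the three waves.

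**Assumptions, because the article gives no figure.** .15 is Cohen's f²; tests are two-sided; arms are 28 and 27; outcome SD is 1 at each wave; the correlation ρ is the same between any two waves, from .3 to .8.

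**1. The plan's own figure.** A noncentral F test with λ = .15 × 55 = 8.25 and one tested coefficient gives power .8051, .8048 and .8045 with one, two and three predictors in total. All round to .805, so the stated figure reproduces. A joint two-degree-of-freedom test would have about .705 at N = 55 and would need 68.

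**2. What the group coefficient estimates.** With balanced data and either ordinary least squares or a random intercept, it is the plain mean of the three arm differences:
- effect (0, d, d): (0 + d + d)/3 = 0.67d
- half lost by T3: (0 + d + 0.5d)/3 = 0.5d
- all lost by T3: (0 + d + 0)/3 = 0.33d

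This does not depend on ρ. With first-order autoregressive errors the lasting-effect figure is lower still: 0.60d at correlation .5 and 0.55d at .8. A simulated data set of 4,000 students with d = 0.775 and ρ = .6 gave a group coefficient of 0.520 (theory 2 × 0.775/3 = 0.516). With group-by-time terms, the same data gave 0.77 at T2 and 0.76 at T3.

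**3. Power at N = 55, lasting effect.** d = 2√.15 = 0.775 and k = 1/28 + 1/27 = 0.0728.
- Group term: mean 2d/3, variance k(1 + 2ρ)/3
- T2 minus T1 contrast: mean d, variance 2k(1 − ρ)
- T2 difference adjusted for T1: mean d, variance k(1 − ρ²)

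At ρ = .3 the noncentrality values are 0.516/0.197 = 2.62, 0.775/0.319 = 2.43 and 0.775/0.257 = 3.01. The noncentral t distribution gives:

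| ρ (assumed) | Group term | T2 minus T1 | T2 adjusted for T1 |
|---|---|---|---|
| .3 | .73 | .66 | .84 |
| .4 | .68 | .73 | .87 |
| .5 | .63 | .805 | .90 |
| .6 | .59 | .88 | .94 |
| .7 | .56 | .95 | .98 |
| .8 | .52 | .99 | >.99 |

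**4. Where the ranking changes.** The group term and the T2 minus T1 contrast have equal power when 8(1 − ρ) = 3(1 + 2ρ), so ρ = 5/14, about .36. Below that the simple change contrast is the weaker of the two. The baseline-adjusted difference beats the group term throughout the range shown; the two are equal when 4(1 − ρ²) = 3(1 + 2ρ), at ρ of about .15.

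**The case against.** The article lists independent variables, not model terms, and an interaction is built from the variables listed. Naming time and group is a common short description of a repeated-measures comparison. The same sentence speaks of the intervention's effect over time, and the hypotheses (reduction with the active module, none with the control) describe a group-by-time pattern. This is also a condensed article, and exact terms and contrasts are often left to a fuller document.

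Much of this stands, and it rules out some stronger readings that a reader might infer:
- **That the protocol prescribes a main-effects-only model.** It never says so; it simply names nothing else.
- **That the group main effect is the test that decides effectiveness.** No sentence names a deciding coefficient.
- **That the sample size shows a main-effect test was planned.** One tested coefficient among one, two or three predictors fits .805 equally well, so a single group-by-time contrast is just as compatible.
- **That any interaction contrast would be more powerful.** Below a correlation of about .36, T2 minus T1 is not.

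What does not stand is that nothing needs correcting. The article does not stay silent on the model: it says specifically which one will be used and lists its independent variables. That description, taken at face value, does not answer the abstract's question. Even on the generous reading, the choice between a group main effect, a T2 contrast, a T3 contrast and a joint test remains open.

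**Conclusion.** The concern holds in conditional form. As written, the model description contains no term for the between-arm difference at T2 or T3. If it is fitted literally, the group coefficient is two thirds of a lasting effect, and one half or one third of the T2 effect if that effect fades. The two-thirds figure is exact for balanced data under equal between-wave correlation or ordinary least squares.

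The power consequence is less certain, because it rests on assumed correlations and on reading .15 as f². Over correlations of .3 to .8 the group term has about .73 to .52 against the stated .805. The gain from correcting the model is dependable over that range only if T1 is used for adjustment. An interaction was probably in mind, so this is a statement to put right before analysis and not proof that the wrong test will be run.

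**What to change.** Amend the model sentence in Statistical analyses and sample size to say that:
- time is a three-level factor and the model includes group-by-time, preferably with arm means constrained equal at T1. Equivalently, T1 enters as a covariate, with T2 and T3 as the only outcome waves;
- the intervention effect is the between-arm difference at T2 and, separately, at T3;
- the group main effect over T1 to T3 is not used to judge effectiveness.

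Carry the same wording into the abstract's Methods. The cost is about one sentence in each place, with no new data. N = 55 still matches a single-coefficient test on the plan's own inputs; it would not cover a joint two-degree-of-freedom test, which needs 68.
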